### Randomization and blinding

Eligible participants will be allocated to one of the four arms using permuted block and stratified randomization by sex (male/female), age group (35–50 and 50–59), and six study sites in a 1:1:1:1 ratio (with 250 participants in each arm). The randomization lists will be generated by an independent statistician, employing block sizes that vary between 8 and 16, which will remain undisclosed to the research team. The randomization lists will be kept in a password-encrypted file, accessible only to an impartial researcher from the research team. This researcher will handle the allocation procedure and communicate the results to the project health coaches via an online portal. The online system will display only de-identified eligible participants, identified by project ID, who have completed the baseline assessments. Each morning during the recruitment phase, this researcher will assign eligible participant to intervention arm according to the randomization lists. Project health coaches will be able to identify their allocated participants as indicated in the online portal. Subsequently, the health coach will schedule the participant’s first intervention session and inform them of their assigned intervention arm. Due to the nature of the intervention, neither participants nor project health coaches will be blinded to the allocation. However, the research team and the principal investigator (PI) will remain blinded to group assignments. Statisticians responsible for data analysis will remain blinded to group assignments until the analysis is complete. Participants who experience serious adverse events (SAEs) during the trial will be unblinded to the PI or research team.

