## Statistical analysis

To address the primary objective, the global comparison test, we will first conduct ANCOVA analysis, using baseline primary outcomes measures (LS7 score) as the covariates and the 6-month measurement as the outcome. For objective 2, we will conduct the same statistical analysis to compare arm 1 (HC + HW) vs arm 4 (waiting group). Similar analyses will be conducted for the other objectives. We will use Bonferroni correction to control the family-wise type I error rate at 0.05.

For exploratory analyses, we will conduct similar analytical plan for the secondary outcomes and subgroup analyses to investigate baseline influence. Post hoc tests will be used to investigate which pairs of levels within a factor differ after an overall (main effect) difference has been established.

We will use linear mixed models (LMMs) to address missing data. LMMs use likelihood-based estimation and are robust in addressing various types of missing data, including missing at random (MAR). Unlike imputation methods, LMMs leverage all information available in the current data, including fixed and random effects which minimizes potential biases related to imputation [82].

Statistical analysis will be performed in R, which is a free-of-charge computer software. Both intention-to-treat (ITT) and per-protocol approach will be used when comparing results across the 4 arms. For the ITT analysis, all randomized participants will be included. For the per-protocol analysis, only participants who have completed all assessments will be included.

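### Randomisation is stratified by sex, age group and site, but the primary ANCOVA names only baseline LS7, so standard errors will be somewhat too large if the strata are prognostic

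*Protocol article*

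**What the plan says.** **Design.** The section Randomization and blinding describes permuted blocks and "stratified randomization by sex (male/female), age group (35–50 and 50–59), and six study sites", allocated equally to four arms, "employing block sizes that vary between 8 and 16". That gives 2 × 2 × 6 = 24 strata.

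**Primary model.** The section Statistical analysis sets out an ANCOVA "using baseline primary outcomes measures (LS7 score) as the covariates and the 6-month measurement as the outcome". For the first pairwise contrast, "we will conduct the same statistical analysis to compare arm 1 (HC + HW) vs arm 4 (waiting group"), and the remaining objectives are handled similarly. On multiplicity: "We will use Bonferroni correction to control the family-wise type I error rate at 0.05".

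**Missing data.** The same section plans linear mixed models and mentions their effects only in general terms ("including fixed and random effects which minimizes potential biases related to imputation"). Sex, age group and site are not listed as terms. Subgroup analyses of baseline influence are mentioned, but as exploratory work that does not change the primary model.

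**The concern.** Stratified blocks force the arms to be nearly equal in sex, age group and site. Where those factors predict the outcome, the forced balance reduces the true sampling variance of the difference between arms. A model that leaves the factors out does not register this: their variance stays in the residual, and the standard error is computed as if the balance had arisen by chance. The analysis then understates the precision that the design achieved.

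This matters somewhat more here than in a two-arm trial. Each of three arms against control is a primary objective, while the power quoted in Sample size calculation is for rejecting at least one of the three nulls. Power for any single comparison is much lower, so a few points are worth having.

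There is also a small defect in the description of the strata: the age bands share the value 50, so the text does not say in which band a 50-year-old was randomised.

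**Working it through.** **Inputs.** From Sample size calculation: difference 0.44, SD 1.57, N = 720 (180 per arm), three comparisons with control, Bonferroni at 0.05, hypotheses written one-sided, stated disjunctive power 0.901, dropout 28%, target 1000. From Randomization and blinding: the 24 strata and block sizes. Assumed, because no document gives it: R², the share of 6-month LS7 variance left after baseline LS7 that the strata explain. The range used is 0 to 0.10. The SD of 1.57 is treated as the residual SD, as the plan's own calculation in effect does.

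**The plan's own figure.**
- Noncentrality m = 0.44 / (1.57 × √(2/180)) = 0.44 / 0.1655 = 2.659.
- Critical value c = z(1 − 0.05/3) = 2.128, one-sided.
- With correlation 0.5 between contrasts (shared control, equal arms), 1 − P(all three Z < c) = 0.9005, against 0.901 stated. It is reproduced.
- 720 / (1 − 0.28) = 1000. It is reproduced.
- Power for one comparison: Φ(2.659 − 2.128) = 0.702.

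**Effect of leaving the strata out.** Under balance within strata, the true variance of the estimate is (1 − R²) times what the unadjusted model reports. Therefore:
- ratio of reported to true standard error = 1/√(1 − R²)
- actual one-sided type I error = 1 − Φ(c/√(1 − R²)), nominal 0.0167
- power, strata omitted = Φ((m − c)/√(1 − R²))
- power, strata included = Φ(m/√(1 − R²) − c)

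| Assumed R² | SE overstated by | Actual type I error | Power, omitted | Power, included |
|---|---|---|---|---|
| 0 | 0% | 0.0167 | 0.702 | 0.702 |
| 0.02 | 1.0% | 0.0158 | 0.704 | 0.711 |
| 0.05 | 2.6% | 0.0145 | 0.707 | 0.726 |
| 0.10 | 5.4% | 0.0124 | 0.712 | 0.750 |

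At R² = 0.10: 1/√0.90 = 1.054; (2.659 − 2.128)/0.949 = 0.560, Φ = 0.712; 2.659/0.949 − 2.128 = 0.675, Φ = 0.750. The difference is 3.8 points. If the tests were run two-sided at 0.05/3, which does not reproduce the stated power, the corresponding figures are 0.610 and 0.659, a difference of 4.9 points.

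**Simulation check** (24 strata, blocks of 8, 12 or 16, 1000 participants, no true effect, 3,000 replicates, adjusted model with one term per stratum). At R² = 0.10, the mean reported standard error was 0.1406 against an actual spread of 0.1330 without the strata, and 0.1334 against 0.1328 with them. The actual spread is almost the same in both models. Only the reported standard error is wrong, and by about the amount the formula gives.

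**Age bands.** Ages 35 to 59 cover 25 single years. If ages were spread evenly (assumed), 1 in 25, or about 40 of 1000, would be aged 50.

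**The case against.** The best defence is that the harm is small and in the safe direction. The estimate is unbiased, type I error is at or below nominal, and the stated 0.901 does not depend on this point. All of that stands.

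Baseline LS7 is the same seven-component score as the outcome, so it already absorbs much of any stable difference by sex, age or site. What counts is the variance left after it, and the documents give no figure. R² could be near zero, and then nothing is lost. This also stands, and it is why the range starts at 0.

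A reader might infer that the design's precision is thrown away, as if 2 to 10% of the sample were lost at R² of 0.02 to 0.10. That equivalence holds for interval width only. The stratified blocks reduce the true variance whether or not the model adjusts, and in power terms the loss equals about 1.6% to 8.0% of the sample.

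A reader might also infer that the stratum of 50-year-olds cannot be recovered. The article does not support that. Allocation followed lists held on file, and Trial status says that recruitment has ended, so each participant's stratum was settled by the list used. The overlap looks like a reporting slip, and it does not touch the primary model as written, which contains no age term.

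Finally, the article is condensed, and it does not say that no other covariate will be used. A fuller analysis plan may add the strata. This carries limited weight: the article does not leave the covariates open but names one, and that model does not match the design it describes.

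**Conclusion.** The point holds as a modest matter of efficiency and clarity, not as a threat to validity. The stated model does not match the stated randomisation. If the strata are prognostic beyond baseline LS7, reported standard errors are too large, intervals too wide and tests conservative.

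For an assumed residual R² of 0 to 0.10, the overstatement is 0 to 5.4%, and the power forgone per comparison is 0 to about 4 percentage points at 180 per arm with one-sided 0.05/3. These figures rest on that assumed range, on 1.57 as the residual SD and on close balance within strata. The standard-error ratio does not depend on sample size. The power figures do, and both powers would be higher if dropout were nearer the 3.8% seen in the cohort than the 28% allowed.

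Nothing in the documents supports a claim of bias or of inflated false positives. The overlap at age 50 is a wording correction.

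**What to change.** State the primary model as 6-month LS7 on arm + baseline LS7 + sex + age group + site, all as fixed effects, taking each participant's stratum as recorded at randomisation. The factors add 1 + 1 + 5 = 7 parameters, which is negligible at this sample size. Name the same covariates in the linear mixed model and in the secondary-outcome models.

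Separately, replace the overlapping age bands with the non-overlapping split that the randomisation lists actually used.

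The cost is one line of model wording and one corrected age range; every variable is already held. Record the change before the statisticians see outcomes by arm, so that the added covariates cannot look data-driven.

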Participants in the HC arm will receive different coaching intensity depending on their NCD risk level (please refer to Table 2 for the definition of NCD risk level). Low-risk and high-risk participants will receive 6 to 10 sessions (co-decided by the participant and the coach), and ≥ 12 sessions during the 6-month intervention period, respectively. In the first coaching session, health coaches will review the participants’ risk profiles and use a 10-point Likert scale to assess their priority, importance, readiness, and confidence to initiate lifestyle changes (higher scores indicate greater priority, importance, readiness, or confidence). The health coach will then employ various skills, adapting to specific situations, to co-design a personalized action plan with specific goals with the participants. Participants will also receive health education through the CORE program to acquire relevant knowledge to achieve these goals. The CORE program covers three topics: physical activity, diet, and mental health. Participants in the HC arm will be assigned to one of these topics, depending on their lifestyle domain risk and their preferences. Follow-up sessions will be conducted face-to-face, via phone, or through text messaging. The participant’s compliance and progress toward the established goals will be continually reviewed, and the action plan will be adjusted as needed.

**Table 2 Tab2:** NCD risk assessment criteria

Assessment metric	Low risk	High risk	Suspected to have NCDs
Health watch	Yes	Yes	Nil
Health coaching	6–10 sessions	At least 12 sessions	Nil
CORE program	Yes	Yes	Nil

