#### Health watch (HW)

Participants assigned to the HW group will receive a Huawei Watch Fit 2 smartwatch (Huawei Technologies Co., Ltd., China). The device tracks various health metrics, including physical activity, daily step counts, and heart rate (HR), serving as an objective tool to assess participants’ overall health status. Participants are encouraged to wear the HW daily. The Huawei Watch Fit 2 underwent internal validation by an optoelectronics expert. The accuracy of SpO2 and HR measurements from Huawei Watch Fit 2 were comparable to those from the COMEN-C502 (Shenzhen Comen Medical Instruments Co., Ltd., China) and the BCI-Autocorr PLUS Digital Pulse Oximeter (Smiths Medical Inc., USA) showing a mean absolute error difference of 2 BPM for HR and 2.2% for SpO2. The HUAWEI Health application, which accompanies the smartwatch, includes built-in workout programs and allows users to set physical activity targets. Participants are required to synchronize their HW with the project cloud. Reminders will be sent to participants who fail to synchronize or without HW data. Technical staff are available via text messaging to assist with any technical issues related to the HW.

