One strength of this study is its large sample size and randomized controlled design, which enhances the reliability and generalizability of the findings. Additionally, the use of the LS7 score and biometric parameters provides a comprehensive evaluation of the participants’ health and lifestyles. However, there are potential limitations to consider. First, we recognize that LS7 score consists of self-reported data on lifestyles and measured body biometrics. The reliance on self-reported data may introduce reporting bias for our primary outcome. Secondly, the effectiveness of HW is more likely to be affected by participant’s adherence and usage to the HW. Similarly, the interaction effect of HC + HW will also be affected. Nevertheless, we will provide technical support to participants and track whether the participants have used the HW. Future studies could explore strategies to enhance adherence and assess the long-term sustainability of the interventions.

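### The per-protocol set is defined only by completing all assessments, so it is a complete-case set that says little about non-adherence

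*Protocol article*

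**What the plan says.** The Statistical analysis section names two approaches: "Both intention-to-treat (ITT) and per-protocol approach will be used when comparing results across the 4 arms". It then defines each set in one sentence. The first is "For the ITT analysis, all randomized participants will be included"; the second is "For the per-protocol analysis, only participants who have completed all assessments will be included". Completion is the only per-protocol criterion given.

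Other sections describe what following the protocol would mean:

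- **Coaching.** Under Health coaching (HC), low-risk participants "will receive 6 to 10 sessions (co-decided by the participant and the coach"; high-risk participants are to have at least 12 over the 6 months.
- **Watch.** Under Health watch (HW), "Participants are encouraged to wear the HW daily". Synchronising with the project cloud is required, and reminders go to those without data.
- **Adherence.** The Discussion gives as its second limitation that "the effectiveness of HW is more likely to be affected by participant’s adherence and usage to the HW". It extends this to the combined arm and says that the team will "track whether the participants have used the HW".

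Under Outcomes measurement, blood tests, blood pressure and anthropometry are taken at baseline and 6 months. The 3-month contact is a shorter questionnaire.

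**The concern.** A per-protocol analysis is normally read as the comparison among people who received what they were assigned. The stated rule selects on something else, namely whether follow-up was complete. It errs in both directions: it admits people who had none of their intervention and removes people who had all of it. Because it selects after randomisation, it can introduce bias without isolating adherence.

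What is at stake is interpretation. Both analyses are to be shown for the four-arm comparisons. If they agree, a reader may take this as evidence that non-adherence did not matter. The rule gives no ground for that, although the article itself lists watch adherence as a limitation and provides for tracking watch use.

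**Working it through.** **1. The rule applied to three kinds of participant**

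| Participant | Received intervention | Both LS7 values | All assessments | In the stated per-protocol set |
|---|---|---|---|---|
| A: no coaching or no watch use, all surveys done | No | Yes | Yes | Yes |
| B: fully adherent, missed only the 3-month questionnaire | Yes | Yes | No | No |
| C: fully adherent, missed the 6-month visit | Yes | No | No | No |

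A and B are both classified against the usual meaning of per-protocol. B's exclusion is not needed for the primary outcome: LS7 requires blood pressure, glucose, cholesterol and BMI, so it can be scored only at baseline and 6 months.

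**2. Size of the set**

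Inputs from Sample size calculation: 720 needed, target 1000, dropout allowed 28%, cohort dropout 3.8%.

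- The plan's own figure: 720 / (1 − 0.28) = 1000. It reproduces.
- At 3.8% dropout: 1000 × (1 − 0.038) = 962, about 96%.
- At 28% dropout: 1000 × (1 − 0.28) = 720, or 72%.

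Both counts reflect dropout only. Missed 3-month questionnaires would lower them. Neither depends on session attendance or watch use.

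**3. What the contrast would estimate**

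Assumptions, not in the documents: the effect is 0.44 (the design difference) in adherers and 0 in non-adherers; a share q of an arm's completers adhere; adherence is unrelated to completion. Then

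contrast among completers = 0.44 × q + 0 × (1 − q) = 0.44q.

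| q | Contrast |
|---|---|
| 0.9 | 0.396 |
| 0.8 | 0.352 |
| 0.7 | 0.308 |
| 0.5 | 0.220 |

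**4. Comparison with intention-to-treat**

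With LS7 at two time points only, someone without a 6-month score adds little to the treatment contrast, whether in ANCOVA on the 6-month value or in a mixed model. The intention-to-treat estimate is thus driven by much the same people. Under the assumptions in step 3 it is also 0.44q, so the two analyses would agree at every q, and their agreement carries no information about q.

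**The case against.** The best defence is that the rule is stated openly and the article never claims that this analysis estimates the effect of adhering. The aim is effectiveness, which the intention-to-treat analysis addresses. On that view the fault is one of labelling. Much of this stands: the fault is that label and content do not match, and the primary analysis is untouched.

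It is also fair to say that an adherence-based set has its own weakness. It would compare self-selected adherers with nearly all controls, since having no trial coaching or watch is almost automatic on a waitlist. Adjustment for baseline LS7 and strata cannot remove confounding by motivation. The low-risk session number is partly chosen by the participant. This is why such a set can only be supportive.

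Four stronger readings are tempting and are not supported:

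- *Adherence is the main threat to the watch effect.* The Discussion lists it second, after self-report bias, and does not rank it as the main one.
- *The two analyses will almost coincide.* That leans on the 3.8% dropout, from a cohort in which everyone received both interventions. The plan allows 28%, waitlist retention is untested there, and if non-adherers drop out more, the completer set is partly enriched for adherers.
- *The estimate will be about 0.31.* That takes one assumed adherence level. The article says the assumed mean came from the cohort, with no restriction to adherers, so 0.44 may already include some dilution. The figures in the working show the mechanism and are not a forecast.
- *Session logs already exist.* Planned numbers and continual review of compliance are stated; recording of attendance is only implied. Tracking of watch use is documented.

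Nor can the point be passed to an unseen analysis plan. Thresholds could be left there, but the article fixes the criterion itself, and fixes it as completion.

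**Conclusion.** The point holds as a mismatch between name and definition. The set described is complete-case: it ignores receipt of the intervention and excludes some participants whose primary outcome is fully observed. It can therefore neither show the effect of adhering nor test robustness to non-adherence.

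Its expected size lies between 72% and 96% of those randomised on dropout alone. The dilution range of 0.40 to 0.22 for 90% to 50% adherence rests on the stated assumptions about effect and completion. The change is worth making because a named analysis would otherwise be misread. It gives no reason to doubt the intention-to-treat primary analysis, the type I error control or the sample size.

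**What to change.** 1. Rename the current set complete-case. For the LS7 analysis, require only the baseline and 6-month LS7 values.
2. If a per-protocol analysis is kept, define it before unblinding by receipt of the assigned intervention:
   - coaching arms: sessions received against the plan's own numbers for the participant's risk level, where attendance is recorded;
   - watch arms: a pre-set minimum of synchronised use, which the investigators must choose because the article gives none;
   - combined arm: both conditions;
   - waitlist arm: no trial coaching or watch before 6 months.
3. Adjust for baseline LS7 and the stratification factors (sex, age group, site).
4. Label the result supportive, stating that adherers are self-selected and the comparison is no longer randomised.

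The cost is a wording change plus use of watch-synchronisation data already provided for. The coaching criterion first needs confirmation that attendance was recorded. The per-protocol set may be smaller.

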## Discussion

This is the first 4-arm RCT that aims to evaluate the effectiveness of HC and HW in encouraging healthy lifestyles that prevent NCD development among at-risk middle-aged individuals. The study design, which includes a combination of HC and HW, HC-only, HW-only, and a waitlist control group, allows a comprehensive assessment of these interventions both individually and simultaneously.

Although both HC and HW have varying degrees of effectiveness for patients with NCDs (including CVD, DM, and HT) in lifestyle modification and disease management [10, 16, 21–24, 29, 30], the evidence supporting the effectiveness of HW is less convincing [83, 84]. Whether the inclusion of HW can enhance the effectiveness of HC remains unknown. Additionally, most prior studies have only recruited patients with NCDs, with fewer studies focusing on populations that are at-risk of NCD development. Recently, significant improvement in HbA1c, body weight, and lipid levels were observed in pre-DM patients after receiving the UK National Health Service Diabetes Prevention Programme (NHS DPP), which involves 9-month intensive lifestyle counseling and behavior-change interventions [25, 85]. However, the absence of a control group and the potential inclusion of participants on medication may have introduced confounding factors, limiting the accurate assessment of the intervention’s effectiveness. The NHS DPP was found to be cost-effective by a few studies [86–88], suggesting that implementing a similar large-scale prevention program could be both beneficial and economical. While the NHS DPP employs nurses, dietitians, and health coaches to deliver interventions, our program relies solely on health coaches, which should reduce intervention costs. Nevertheless, we must also consider the mode, frequency, and duration in delivering the intervention.

The anticipated findings from this RCT could have significant implications for public health strategies aimed at preventing NCDs. Similar to other developing regions, the Hong Kong government recognizes the significance of primary health care and has implemented the Co-Care pilot scheme to enhance awareness and screening for HT, DM, and hypercholesterolemia [89]. By demonstrating the effectiveness of HC and HW, either alone or in combination, this RCT will provide a standardized, scalable, and sustainable lifestyle intervention that can be integrated into routine primary care clinical practice, specifically targeting at-risk populations. The use of wearable technology for continuous health monitoring, coupled with personalized HC, may offer an expandable and sustainable approach to promoting healthy lifestyle changes. This could reduce the burden on healthcare systems by lowering the incidence of NCDs and decreasing the need for medical interventions and hospitalizations [90]. In the future, a cost-effectiveness analysis may be conducted to estimate the reduce in the healthcare burden arose from preventing NCDs, showing a long-term economic impact of implementing HC and HW. The future cost reduction could be induced from a lower rate of high blood glucose level, high BP, and 10-year CVD risk of the intervention arms compared to the control group with the application of simulation model [91–93]. The necessary variables could be directly obtained from the biometric parameters and QRISK3 score measured in this study. These findings could inform policy-making, leading to the development of guidelines and programs that leverage technology and personalized coaching to enhance public health outcomes. The success of such interventions could also stimulate further research into the long-term benefits and cost-effectiveness of integrating wearable devices and HC into preventive healthcare. This evidence-based approach may advocate for broader adoption and funding of similar programs globally, ultimately contributing to the reduction of NCDs on a larger scale.

One strength of this study is its large sample size and randomized controlled design, which enhances the reliability and generalizability of the findings. Additionally, the use of the LS7 score and biometric parameters provides a comprehensive evaluation of the participants’ health and lifestyles. However, there are potential limitations to consider. First, we recognize that LS7 score consists of self-reported data on lifestyles and measured body biometrics. The reliance on self-reported data may introduce reporting bias for our primary outcome. Secondly, the effectiveness of HW is more likely to be affected by participant’s adherence and usage to the HW. Similarly, the interaction effect of HC + HW will also be affected. Nevertheless, we will provide technical support to participants and track whether the participants have used the HW. Future studies could explore strategies to enhance adherence and assess the long-term sustainability of the interventions.

